**1. Summary**

Table 1. Summary of the trial characteristics

|                                       |                                                                                                                                                                                                                                                                                                                                                                                                                                                   |
|---------------------------------------|---------------------------------------------------------------------------------------------------------------------------------------------------------------------------------------------------------------------------------------------------------------------------------------------------------------------------------------------------------------------------------------------------------------------------------------------------|
| Sponsor                               | INCLIVA                                                                                                                                                                                                                                                                                                                                                                                                                                           |
| Title                                 | Impact of Self-monitoring of Blood Pressure and Self-titration of Antihypertensive Medication in the Control of Hypertension and Adherence to Treatment. A Pragmatic, Randomized, Controlled Clinical Trial (ADAMPA Study).                                                                                                                                                                                                                       |
| Protocol Code                         | ADAMPA                                                                                                                                                                                                                                                                                                                                                                                                                                            |
| Principal Investigators               | 
[name]
Centro de Salud de Nazaret
Departamento de Salud de Valencia Clínic-La Malvarrosa
[contact]
Email: [contact]
 
[name]
Health Services Research Unit
Center for Public Health Research (CSISP-FISABIO)
[name]
[contact]
Email: [contact]
                                               |
| Centers                               | Primary care centers from the Valencia Clínic-La Malvarrosa Health District, Conselleria de Sanitat de la Comunitat Valenciana                                                                                                                                                                                                                                                                                                                    |
| IRB                                   | The clinical research ethics committee from Hospital Clínico Universitario de Valencia (CEIC-HCUV)                                                                                                                                                                                                                                                                                                                                                |
| Monitoring responsible                | Spanish Clinical Research Network (SCReN).                                                                                                                                                                                                                                                                                                                                                                                                        |
| Intervention                          | 
 
Intervention group: The intervention consists of self-monitoring blood pressure at home, and subsequent medication self-titration, based on a medication adjustment plan pre-established by the family physician, in patients with uncontrolled hypertension.
 
Control group: Patients in this arm will receive routine care for high blood pressure in the primary health care center.
 
 |
| Clinical trial phase                  | Phase IV                                                                                                                                                                                                                                                                                                                                                                                                                                          |
| Objectives                            | To evaluate the comparative effectiveness of an intervention that includes educational components, self-monitoring of blood pressure and self-titration of antihypertensive medication in the improvement of control of hypertension compared to usual care in a poorly controlled population of hypertensive patients.                                                                                                                           |
| Design                                | Pragmatic, controlled, randomized, non-masked clinical trial with two parallel arms.                                                                                                                                                                                                                                                                                                                                                              |
| Disease                               | Hypertension                                                                                                                                                                                                                                                                                                                                                                                                                                      |
| Primary outcome measure               | Difference in mean systolic blood pressure, in mmHg. At 12 months of follow-up between the intervention and control groups, determined at physicians' practice with a validated automatic electronic sphygmomanometer.                                                                                                                                                                                                                            |
| Participants                          | Patients assigned to the Valencia Clínic-La Malvarrosa Health Department. Total number of patients to be randomized: 458 (229 per arm).                                                                                                                                                                                                                                                                                                           |
| Treatment duration                    | 12 months (also, a pragmatic extension with passive follow-up is planned for 24 months, collecting a reduced set of outcome variables, as secondary variables)                                                                                                                                                                                                                                                                                    |
| Calendar and expected completion date | The trial will take place over 3 years (6 months of recruitment, 12 months of follow-up for the main analysis of results, 12 months of pragmatic follow-up at 24 months, and finally 6 months for reporting results). Estimated Completion Date: 2020.                                                                                                                                                                                            |

#### ANNEX 1. Serious Adverse Event Reporting Form

### **3. GENERAL INFORMATION**

#### **3.1 Trial identification**

Title: Impact of Self-monitoring of Blood Pressure and Self-titration of Antihypertensive Medication in the Control of Hypertension and Adherence to Treatment. A Pragmatic, Randomized, Controlled Clinical Trial (ADAMPA Study).

Protocol code: ADAMPA

EudraCT number: 2016-003986-25

Clinicaltrials.gov

#### **3.2 Trial design**

Pragmatic, controlled, randomized, non-masked clinical trial with two parallel arms.

##### **3.5.3 Clinical researchers (MEFI)**

Forty-seven researchers, clinical family doctors, distributed in 17 Basic Health Areas and in 21 Primary Care Centers (Health Centers and Auxiliary Centers). Department Valencia Clínic- La Malvarrosa. INCLIVA Health Research Institute.

## **4. Background**

The presence of hypertension is one of the most important issues in the global burden of disease (1). In developed countries, the degree of control of hypertension has increased progressively over the last 15 years and has contributed to a decline in cardiovascular morbidity and mortality (2-8). However, a recent study carried out in 12 European countries showed that more than 50% of patients treated for hypertension continued to have uncontrolled blood pressure (BP) (9) and that results are far from ideal. As a large part of hypertension management is carried out in primary care (PC) and it is one of the most prevalent problems encountered by General Practitioners (GP), interventions aimed at improving its management should preferably be made in this setting. Recent hypertension clinical guidelines put emphasis on self-measured blood pressure monitoring (SMBP) by patients and on team-based systems to manage the condition (10).

Self-measured blood pressure monitoring at home (SMBP) is practiced extensively nowadays. In the United Kingdom and Canada it is highly recommended by GPs and used by more than 30% of patients (11, 12). Systematic reviews have shown disparate information regarding the effectiveness of SMBP alone in reducing blood pressure (BP). On the other hand, self-monitoring in conjunction with co-interventions (including systematic medication titration by doctors, pharmacists, or patients; education; or lifestyle counseling) has been shown to lead to clinically significant BP reduction, which persists for at least 12 months. Nevertheless, the effectiveness of SMBP requires additional evaluation given that its definition in those studies is highly heterogeneous (different clinical protocols, different strategies for additional support and management) and given the fact that most studies have short follow-ups (1 year or less) (13,14).

Regarding home titration of antihypertensive medication, evidence is more limited and shows mixed results. Two clinical essays, the TASMINT2 (15) and the TASMINT-SR (16), both in the United Kingdom and developed in the primary care setting by the same research team, are some of the most recent and interesting clinical trials carried out in this field. In these studies, SMBP together with self-titrate medications (according to a previously agreed plan), combined with telemedicine components, was compared with usual care. In both studies systolic blood pressure (SBP) decreased from baseline to 12 months, with significant differences between the intervention and control group (5.4 and 9.2 mmHg, respectively). Frequency of side effects was similar in both groups (15,16). The TASMINT-SR study is of special relevance because it was carried out with high-risk patients (with a personal history of stroke, ischemic cardiopathy, diabetes or kidney failure), a population of special interest to achieve BP targets (16). On the other hand, a clinical trial carried out in the US in a low-income, predominantly minority population, aimed to determine whether health coaching, SMBP and home titration of antihypertensive medications could improve BP control compared with SMBP and health coaching alone. The results showed that both the home-titration arm and the no-home-

titration arm had a reduction in SBP, with no significant differences between them from baseline to 6 months (17).

Finally, when interpreting hypertension studies over time, it is important to proceed with caution, as the definition of the condition changes almost with every update of guidance. For instance, earlier versions of guidelines such as those of the Joint National Committee (JNC) and of the European Society of Hypertension (ESH)/European Society of Cardiology (ESC), suggested more restrictive BP control objectives than recent versions (especially in patients over 60 years old, diabetics and patients with renal failure)(18-20). These objectives may be modified again in the light of the results of recent studies (21-23).

## **5. HYPOTHESIS AND OBJECTIVES**

### **5.1 Hypothesis**

The starting hypothesis of the trial is that an intervention of self-monitoring and self-adjustment of the medication in hypertensive patients may allow an improvement in the management of these patients with respect to usual clinical practice.

### **5.2 Objectives**

1. To evaluate the effectiveness of an intervention based on self-monitoring and self-adjustment of medication in poorly controlled hypertensive patients.
2. Evaluate its impact on adherence to treatments, lifestyles, quality of life, the occurrence of adverse events, the use of health services, and the costs of care.
3. Estimate its efficiency (cost-effectiveness).
4. Evaluate the views and experiences of patients, caregivers and health professionals about self-management, self-monitoring and self-adjustment of antihypertensive medication

## **6. DESIGN**

### **6.1 Outcome measures**

#### **6.1.1 Primary outcome measure**

Difference in mean systolic blood pressure, in mmHg. At 12 months of follow-up between the intervention and control groups, determined at physicians' practice with a validated automatic electronic sphygmomanometer.

At least 2 measurements should be taken in the sitting position, spaced 1-2 minutes apart, or an additional measurement if the first 2 are quite different. The average of the 2 measurements taken as valid will be considered as TA.

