### **6.3.2 Masking**

Due to the nature of the intervention, it is not feasible to blind the study for either the patients or the Research Family Physicians (MEFI), who are responsible for the patients. Likewise, the Collaborating Research Physicians (MIC), who will conduct the training interventions in the first year and collaborate with MEFI in follow-up visits, cannot be blinded

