#### **6.5 Patients follow-up**

The follow-up of the patients will be conducted by the MEFIs in line with routine clinical practice conditions. MEFIs will be responsible for patient selection and inclusion in the trial and will execute the training actions as outlined in point 6.4.

Additionally, the MIC team will reinforce the training and information actions specified by the MEFI and defined in point 6.4. However, it's important to note that the MIC team will not make clinical decisions or modify the management or recommendations of the MEFI. They will also handle data collection during the scheduled visits in the study, including the baseline visit and follow-up visits at 6 and 12 months, working in collaboration with the MEFI.

In the first 12 months of the study, the MIC team will conduct bi-monthly telephone reinforcement sessions. These sessions aim to contact patients in the intervention group with the goal of improving adherence to the intervention and addressing any potential concerns.

In the second year (passive or pragmatic follow-up), patient follow-up will be aligned as closely as possible with routine management in usual clinical practice. Therefore, the role of the MIC will be carried out by a nurse

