\*Blood pressure; \*\* Smoking habit, exercise, BMI; \*\*\*Information relative to the previous year. Its determination will be made at the health center with a validated automatic electronic sphygmomanometer. At least 2 measurements will be taken in a seated position, spaced at 1-2 minutes, and another additional measurement if the first 2 are very different. The average of the measurements taken will be recorded (8).

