## **9. EFICACY ASSESSMENT**

### 9.1 Efficacy variables and evaluation methods

**Table 4. Efficacy variables (comparative effectiveness) of the ADAMPA study**

| VARIABLES                                                                                                                                                                                           | EVALUATION METHODS                                                                                                                                                                                                                                                                                                                                      |
|-----------------------------------------------------------------------------------------------------------------------------------------------------------------------------------------------------|---------------------------------------------------------------------------------------------------------------------------------------------------------------------------------------------------------------------------------------------------------------------------------------------------------------------------------------------------------|
| Primary outcome measure                                                                                                                                                                      |                                                                                                                                                                                                                                                                                                                                                         |
| Difference in mean systolic blood pressure (SBP), in mmHg at 12 months of follow-up between the intervention and control groups.                                                                    | It will be determined at physicians' practice with a validated automatic electronic sphygmomanometer.

At least 2 measurements will be taken in a seated position, spaced at 1-2 minutes, and another additional measurement if the first 2 are very different. The average of the measurements taken  will be considered as SBP/DBP. |

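### The protocol gives two scoring rules for the primary blood pressure endpoint; they differ whenever a third reading is taken, and one lets unmasked staff choose which readings count

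*Protocol*

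**What the plan says.** The primary endpoint is the between-arm difference in mean office systolic pressure at 12 months, measured with a validated automatic device. How several readings become one value is stated in four places, in two ways.

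- Section 6.1.1 asks for at least two seated readings, "or an additional measurement if the first 2 are quite different", and then states: "The average of the 2 measurements taken as valid will be considered as TA". Table 3 (section 8.5.1) repeats this.
- Table 4 (section 9.1), in the primary outcome row, asks for "another additional measurement if the first 2 are very different. The average of the measurements taken" and takes that average as the SBP/DBP. The footnote to Table 2 (section 6.6) agrees: "The average of the measurements taken will be recorded".

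No place gives a figure in mmHg for the disagreement that calls for a third reading, or says what makes a reading valid.

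Section 6.3.2 says that neither the family physicians (MEFI) nor the collaborating physicians (MIC) can be blinded; of the latter it says that those who "collaborate with MEFI in follow-up visits, cannot be blinded". Section 6.5 gives the visit data to the same people. Of the MIC team it says: "They will also handle data collection during the scheduled visits in the study, including the baseline visit and follow-up visits at 6 and 12 months". No masked outcome assessor is described.

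**The concern.** Both wordings are current text for the same endpoint, so an analysis plan cannot follow both. With a third reading, one rule averages two values and the other averages three.

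The two-reading rule also leaves two decisions to whoever measures: whether the first two readings disagree enough to repeat, and which two of three to keep. Those people know the arm, and they deliver or reinforce the intervention. An automatic device protects each reading but not the choice among readings. If that choice leaned with the arm, even without intent, the lean would enter the treatment contrast directly. The same text governs the secondary systolic and diastolic outcomes and the percentage of patients controlled.

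**Working it through.** **1. The plan's own figure.** Section 11.1 uses a difference of 5 mmHg, SD 15 mmHg, two-sided alpha 0.05 and 90% power. The normal formula gives n per arm = 2 × (1.960 + 1.282)² × 15² / 5² = 189.1, so 190 per arm and 380 in total. The noncentral-t version gives 191 per arm, which is the plan's 382 (power 0.901). Then 382 × 1.20 = 458.4, the plan's 458. The sample size is not in question. It supplies the 5 mmHg yardstick and the standard error used below.

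**2. The two rules on one visit.** Take illustrative readings of 158, 144 and 142 mmHg.

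- All readings taken: (158 + 144 + 142)/3 = 148.
- Two valid readings: (144 + 142)/2 = 143, (158 + 142)/2 = 150 or (158 + 144)/2 = 151, depending on the pair.

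The two-reading rule spans 151 − 143 = 8 mmHg for one patient at one visit.

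**3. What selection could do to an arm mean.** The protocol gives neither a within-visit SD nor a trigger, so both are assumptions: SD (σ) 4, 6 or 8 mmHg, and a third reading when the first two differ by more than c = 5 or 10 mmHg. Readings are taken as independent and normal; 1,000,000 visits were simulated for each setting.

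- Probability of a third reading: P = 2 × [1 − Φ(c / (σ√2))]. For σ = 4 and c = 5 this is 2 × [1 − Φ(0.884)] = 0.377, as simulated.
- Shift at a visit with three readings, lowest pair against all three: (mean of three − highest)/2.
- Shift in the arm mean: P × that shift.

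| σ (mmHg) | Trigger (mmHg) | P (third reading) | Mean shift at those visits (mmHg) | Shift in arm mean (mmHg) |
|---|---|---|---|---|
| 4 | >5 | 0.377 | −2.33 | −0.88 |
| 4 | >10 | 0.077 | −3.20 | −0.25 |
| 6 | >5 | 0.555 | −3.13 | −1.74 |
| 6 | >10 | 0.239 | −3.89 | −0.93 |
| 8 | >5 | 0.659 | −3.96 | −2.61 |
| 8 | >10 | 0.376 | −4.66 | −1.75 |

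The smallest arm shift is 0.077 × 3.20 = 0.246 and the largest is 0.659 × 3.96 = 2.61, so about 0.2 to 2.6 mmHg. Every row assumes that the lowest pair is chosen at every three-reading visit in one arm, while the other arm is scored without bias.

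**4. Neutral choices.** If the closest pair is always kept, its mean difference from the all-readings average at three-reading visits is between −0.02 and 0.01 mmHg, which is zero to simulation error. Only noise is added: the SD of that difference is 2.8 to 5.6 mmHg. The all-readings average with a fixed trigger is likewise unbiased (between −0.01 and 0.01 mmHg).

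**5. Consequence for the test.** With 191 per arm, SE = 15 × √(2/191) = 1.53 mmHg. With no true effect, a spurious shift of 0.9 mmHg (close to the row with σ = 6 and c = 10) raises the two-sided false-positive rate from 5% to 9.0%. A shift of 0.5 mmHg gives 6.2%, and 1.9 mmHg gives 23.6%.

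**The case against.** The strongest reply is that the conflict is shorthand. The sentences in the four places are nearly the same and rest on the same guideline, so the wording in Table 4 and the Table 2 footnote may only abbreviate that of 6.1.1, with *valid* meaning that the discordant reading is dropped. On that reading the choice is neutral and step 4 shows no mean bias. This limits the likely harm but does not settle the text: no place says which readings are valid, and the primary outcome row of Table 4, read literally, averages all of them.

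It also stands that only visits with a third reading are affected, that the device is automatic, and that nothing shows staff would select by arm. A numeric trigger and the CRF layout could sit in a measurement manual, so their absence alone is no error.

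Three stronger readings are tempting, and the protocol supports none of them.

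- *That this is the only route by which the endpoint could drift by arm.* Rest time, cuff size and reference arm (Table 3) also depend on the operator, and the complete-case analysis (7.4, 11.2) is a further route.
- *That the value could never be re-scored because only an average is kept.* The Table 2 footnote says that the average is recorded, not that single readings are discarded. Section 12.4 requires CRF entries to be verifiable against source documents and primary endpoint data to be fully verified. That does not prove that each reading survives, but it rules out asserting the opposite.
- *That opposite leanings in the two arms are to be expected.* Low pairs in one arm and high pairs in the other would move the contrast by 0.5 to 5.2 mmHg in the simulation, but nothing in the protocol points to such behaviour.

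**Conclusion.** The point holds as an internal contradiction in the definition of the primary endpoint. That part needs no assumption: 6.1.1 and Table 3 state one rule, Table 4 and the Table 2 footnote another. The rules part whenever a third reading is taken, and the first gives undefined discretion to unmasked staff. The protocol does not name who operates the device at 12 months, but everyone to whom it assigns data collection knows the arm.

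The size does rest on assumptions. The range of about 0.2 to 2.6 mmHg is 5% to 52% of the 5 mmHg design difference (0.25/5 and 2.61/5). It is a bound under consistent selection of the lowest pair in one arm, not a forecast; under a neutral choice the mean bias is zero. The wording should be corrected because the exposure falls on the primary endpoint and the correction is cheap.

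**What to change.** State one rule in 6.1.1, the Table 2 footnote, Table 3 and Table 4 that leaves the assessor no choice. One example is SBP and DBP as the mean of all readings taken, with a fixed mmHg difference that triggers the third reading. The trigger belongs with the rule: averaging all readings removes the choice of subset but not the choice of when to repeat. Enter each reading in the CRF in the order taken, and compute the average from those entries, so that the score can be audited and checked in a sensitivity analysis.

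The cost is wording in four places and two or three CRF fields. The sample size stays at 382, or 458 with the allowance for loss.
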